### Breaking of the study blind

The study blind will be broken after all participants have finished part 1 of the study. In case of emergencies (serious adverse events, suspected unexpected serious adverse reactions), the blind will be broken after consultation of the principal investigator. Subsequently, these events will be reported to the Medical Ethical Committee.

### Intervention

#### Metformin

After randomisation, all participants will receive either metformin 500 mg tablets or identical placebo tablets. Medication is given according to an increasing dosage regimen. In week 1, participants take 1 tablet daily. Every week, dosage increases with 1 tablet, reaching a maximum of 4 tablets in week 4. This maximum dose will be administered till the end of part 1.

In case the participant develops gastro-intestinal symptoms, dosage will be reduced to the last well-tolerated dosage. Participants will be asked to return remaining study medication every visit. Pill counts will be performed by a research assistant.

During the follow-up study, metformin will be administered according to the dosage regimen of part 1.

### Physical training

During part 1 of the study, physical training will be offered in groups, supervised by a physiotherapist. Training sessions will be twice weekly, and last for one hour. The main goals are creating pleasure in physical exercise, improvement of endurance and coordination. Attendance at the training will be recorded.

All participants will perform a standardised fitness test at study entry, halfway part 1 and at the end of parts 1 and 2.

### Statistical analysis

Data will be analysed using IBM SPSS Statistics. Baseline data will be reported as descriptive statistics. Normally distributed data will be reported as mean ± SD and nonparametric data as median (range).

### Efficacy of metformin

To assess the effect of metformin versus placebo, the Students T test will be used to compare means of normally distributed data and the Mann-Whitney U test to compare nonparametric data. The χ^2^ test will be used for dichotomous outcomes (the development of impaired fasted glucose, impaired glucose tolerance, T2DM, and the presence of micro- and macro- vascular complications versus the study groups).General linear models (analysis of repeated measures) or mixed models (if too much data is missing) will be used to determine the therapeutic effect of the drug. After part 2 of the study, comparisons will be made between the four subgroups (metformin in part 1 and part 2; metformin in part 1 and no medication in part 2; placebo in part 1 and metformin in part 2; placebo in part 1 and no medication in part 2) (Figure 
1).

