### Participants

Recruitment of participants takes place at the paediatric outpatient clinics of the study centres. Patients are eligible for this study if they meet the inclusion and exclusion criteria as listed in Table 
1. Informed consent will be obtained from all participants/parents or caretakers.

**Table 1 T1:** Inclusion and exclusion criteria

**Inclusion criteria**	**Exclusion criteria**
Age: 10–16 years	Presence of T2DM, polycystic ovarian syndrome, or endocrine disorders treated with corticosteroids
Obesity defined as BMI standard deviation score >2.3	Height <-1.3 SD of target height
Insulin resistance defined as HOMA-IR ≥3.4	Syndromal disorders with or without mental retardation
Caucasian descent	Pregnancy
Informed consent signed by parents and participant	Use of anti-hyperglycaemic drugs, ritonavir or ACE-inhibitors
	(History of) alcohol abuse
	Impaired renal or hepatic function (renal function defined as glomerular filtration rate (GFR) <80 ml/min; GFR = 40 × length (cm)/serum creatinine (μmol/l); hepatic function: alanine aminotransferase >150% of normal value for age)
	Insufficient knowledge of Dutch language

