### Sample size

A power analysis for reduction in BMI (primary endpoint) and for reduction of insulin resistance calculated by the HOMA-IR has been performed. For BMI, a sample size of 47 participants per group (metformin and placebo) is sufficient to detect a change in BMI of 2.94% with 90% power. Sample size for HOMA-IR was calculated using a simulation based on retrospective data available from our obesity out-patient clinic. Group sample sizes of 60 patients in both groups were found sufficient for the detection of a difference of 1.6 with a significance level of 0.05. To prevent inadequate power due to drop out of participants, 20% more patients will be included. This means a total amount of 144 children and adolescents have to be included in the study.

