### Randomisation

Subjects will be assigned to metformin or placebo in accordance with a randomisation schedule generated by the department of Clinical Pharmacy of the St Antonius Hospital, using PASW Statistics 18.0. Randomisation will be done in blocks of 20 subjects assuring a balanced study after each 20 consecutive inclusions per research site. All research staff is blinded for treatment allocation during the time of the study. Randomisation lists will be kept under secured access in the clinical pharmacy department of both participating hospitals.

The research physician assigns included participants to consecutive study numbers, which correlate with the randomisation and medication number.

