### Physical examination and anthropometrics

Every visit, except at week 3 and 5, anthropometric measurements are performed. These include: height, weight, and waist, hip, neck, and right wrist circumference.

Height will be measured with a digital stadiometer in the St Antonius Hospital, and with an analogue stadiometer at the Jeroen Bosch hospital. Height will be recorded to the nearest 0.1 cm.

Weight is recorded on a digital scale in all study centres, and is recorded to the nearest 0.05 kg. Waist, hip, neck, and right wrist circumferences are measured with the same tape-measure in both centres, by the research physician. All measurements are recorded to the nearest 0.1 cm. Waist circumference is measured at the level of the navel and hip circumference at the level of the anterior superior iliac spine. Neck circumference is measured three times, the smallest circumference is recorded. Circumference of the right wrist is measured at the level of Lister’s tubercle.

Blood pressure and heart rate are measured with subjects in a seated position using a cuff appropriate for the participants’ arm circumference. In both study centres, blood pressure will be measured electronically.

During the visits in weeks 0, 37, 73, and 146, an extended physical examination is performed by the research physician. This examination includes auscultation of heart, lungs, and abdomen, and abdomen palpation. Abnormal findings will be recorded. The skin will be examined for the presence of acanthosis nigricans, striae, acne, and, in girls, hirsutism. For all participants, pubertal stage according to the classification of Tanner will be recorded. In girls, this includes development of the breasts and pubic hair; in boys, stage of pubic hair and testicular volume is estimated.

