### Primary endpoints and measures

Primary study endpoint for efficacy of metformin is the reduction in BMI standard deviation score, which is calculated from the anthropometric measurements, and the reduction of insulin resistance calculated by the HOMA-IR.

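### The plan names an unadjusted t or Mann-Whitney test beside a repeated-measures or mixed model, makes neither primary and fixes no baseline or site term; a baseline- and site-adjusted primary analysis would be at least as precise in large samples.

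*Protocol article*

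**What the plan says.** In the protocol article, section Efficacy of metformin, the effect of metformin against placebo is assessed as follows: "the Students T test will be used to compare means of normally distributed data and the Mann-Whitney U test to compare nonparametric data". After a sentence on dichotomous outcomes, the same paragraph adds general linear models for repeated measures, "or mixed models (if too much data is missing) will be used to determine the therapeutic effect of the drug". It does not rank the two families of analysis and lists no covariates for the models.

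Other sections bear on this:

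- Primary endpoints and measures: "Primary study endpoint for efficacy of metformin is the reduction in BMI standard deviation score", together with "the reduction of insulin resistance calculated by the HOMA-IR". Both are changes from baseline.
- Randomisation: "Randomisation will be done in blocks of 20 subjects assuring a balanced study after each 20 consecutive inclusions per research site". Site therefore acts as a stratum.
- Tables 2 and 3: physical examination and an oral glucose tolerance test with a fasting sample take place at week 0 and week 73, so BMI-SDS and HOMA-IR are available at the start and end of part 1.
- Table 1: "Insulin resistance defined as HOMA-IR ≥3.4" is an entry criterion.

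**The concern.** Neither a t test nor a Mann-Whitney test takes a covariate. Applied to change, the t test fixes the slope on baseline at 1, whereas ANCOVA estimates that slope from the data. Participants are selected for a high HOMA-IR, so values can be expected to regress towards the mean, and a slope of 1 is then likely to be too steep. Site is used to balance the arms but does not appear in the test, so any between-site variance in the outcome stays in the error term.

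Two further weaknesses lie in the same paragraph. The choice between t and Mann-Whitney depends on the distribution observed; if HOMA-IR is skewed and Mann-Whitney is chosen, that test gives no mean difference to set against the 1.6 used in the sample size section. And with two overlapping families of efficacy analysis and no hierarchy, the analysis that carries the conclusion can be settled after the data are seen.

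At stake are wider confidence intervals than the collected data require, and a primary result that is not tied to one pre-stated model.

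**Working it through.** **The plan's own figure.** The HOMA-IR calculation gives 60 per group, and 20% is added: 60 × 1.2 = 72 per arm, 2 × 72 = 144. This matches the stated total. The BMI calculation ("a sample size of 47 participants per group (metformin and placebo) is sufficient to detect a change in BMI of 2.94% with 90% power") gives no SD and cannot be checked. For HOMA-IR no SD and no power are stated. No correlation between baseline and follow-up and no site variance are given for either endpoint.

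**Inputs that must be assumed.** The correlation rho between baseline and follow-up, 0.3 to 0.9; the ratio k of baseline SD to follow-up SD, 0.7 to 1.3; the site share of outcome variance, 0 to 10%; a starting power for HOMA-IR of 80% or 90%, two-sided alpha 0.05.

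**Formulas (large sample, 1:1 allocation), per unit of follow-up variance.**

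- Change-score t test: 1 + k² − 2·rho·k
- ANCOVA: 1 − rho²
- Difference between the two: (1 + k² − 2·rho·k) − (1 − rho²) = (k − rho)², which is never negative. ANCOVA is therefore never less precise, and the two are equal when k = rho.
- With k = 1 the ratio is (1 − rho²) / (2(1 − rho)) = (1 + rho)/2.
- Power after adjustment: Φ((1.96 + z_power)/√ratio − 1.96), with z_power = 0.84 for 80% and 1.28 for 90%.

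**Equal variances (k = 1).**

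| rho | ratio | n equivalent to 60 per group | 80% power becomes | 90% power becomes |
|---|---|---|---|---|
| 0.3 | 0.65 | 39 | 93.5% | 98.0% |
| 0.5 | 0.75 | 45 | 89.9% | 96.3% |
| 0.7 | 0.85 | 51 | 86.0% | 94.0% |
| 0.9 | 0.95 | 57 | 82.0% | 91.4% |

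**Unequal variances.**

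- k = 0.7, rho = 0.5: 0.75 / (1 + 0.49 − 0.70) = 0.75/0.79 = 0.95
- k = 0.7, rho = 0.7: 0.51 / (1 + 0.49 − 0.98) = 0.51/0.51 = 1.00, no gain
- k = 1.3, rho = 0.5: 0.75 / (1 + 1.69 − 1.30) = 0.75/1.39 = 0.54
- k = 1.3, rho = 0.7: 0.51 / (1 + 1.69 − 1.82) = 0.51/0.87 = 0.59

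**Site.** Adjusting for site multiplies the variance by 1 minus the site share: 1.00 for a share of 0, 0.95 for 5%, 0.90 for 10%. In terms of 60 per group that is 60, 57 and 54.

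**Cost in degrees of freedom.** With 60 per arm the t test has 120 − 2 = 118. One baseline slope and one term for two hospitals leave 116.

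**The case against.** The strongest reply has four parts.

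First, the t and Mann-Whitney tests are not the whole efficacy analysis. The repeated-measures or mixed model is named in the same paragraph, and it may include the baseline visit and other terms. A reader who stops at the first sentence might infer that an unadjusted test is the only comparison and that baseline is ignored. The article does not support that: the models are there, and a reduction already uses baseline.

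Second, the size of the gain is not established. Rho, the variances and the HOMA-IR power are all absent. Truncating baseline HOMA-IR at 3.4 makes equal variances doubtful, and the working shows a case with no gain at all. A much larger saving can be obtained by comparing ANCOVA with a t test on follow-up values (ratio 1 − rho², or 0.19 at rho 0.9), but that comparison does not fit endpoints defined as reductions.

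Third, site may matter little. At one hospital "Height will be measured with a digital stadiometer" and at the other with an analogue one, from which a reader might infer substantial site noise in BMI-SDS. A constant offset between instruments largely cancels in a within-person change, and all blood samples go to one laboratory.

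Fourth, covariates are commonly left to a full protocol or analysis plan, and neither is shown.

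The first three parts stand and limit the wording and the size. The fourth stands only in part: the article does not merely leave the analysis open but states a test that takes no covariate as the way to assess the effect, so an analysis plan that followed it would inherit the weakness.

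**Conclusion.** The point holds as one of efficiency and of an unfixed primary analysis. It does not show invalidity. Leaving out a randomisation stratum tends to make the test conservative, so type I error is not inflated on that account. Regression to the mean after entry at a high HOMA-IR acts on both randomised arms alike, so it does not bias the comparison.

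Against a change-score t test, baseline adjustment lowers the variance by 5% to 35% for rho from 0.9 down to 0.3, provided baseline and follow-up variances are equal. For an outcome as stable as BMI-SDS may be (rho 0.8 to 0.9, assumed) that is only 5% to 10%. With unequal variances the gain ranges from nothing to more than this. The power figures depend on an assumed starting power. The gain from site is at most its share of the variance and may be close to zero. What needs no assumed correlation or variance ratio is the direction: in a large 1:1 trial, ANCOVA is never less precise than the t test on change.

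**What to change.** For BMI-SDS and HOMA-IR at the end of part 1 (week 73), name one primary analysis per endpoint: ANCOVA, or the mixed model already mentioned evaluated at that visit, with treatment, baseline value and site as terms. Fix this choice in advance, so that it depends neither on the observed distribution nor on an unquantified amount of missing data. Analyse HOMA-IR on the log scale and report the adjusted geometric mean ratio with its 95% confidence interval; add a mean difference on the original scale so that the result can be related to the planned 1.6. Keep the t and Mann-Whitney tests as supportive analyses.

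The cost is a few degrees of freedom (118 to 116 in the working above) and a ratio scale for HOMA-IR that differs from the planning scale. No new data are needed, since baseline values and site are already recorded. When the article appeared, 60 participants had been included and 13 had finished part 1, and the blind is kept until all have finished part 1, so the change could be made before any unblinded comparison.

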## Background

The prevalence of obesity in adolescents is increasing rapidly, having a significant impact on both physical and psychosocial health
[1]. Currently, the worldwide prevalence of obesity in children and adolescents is 2% to 3%, using the International Obesity Taskforce standard definition for paediatric obesity in children and adolescents 5 to 17 years of age
[2]. In the Netherlands, the prevalence of obesity in children and adolescents (4–15 years) of Dutch descent is 1.8% in boys and 2.2% in girls. In Turkish boys and girls, these numbers are higher, 8.4% and 8.0%, respectively
[3].

In obese children and adolescents, insulin resistance, impaired fasting glucose, impaired glucose tolerance, dyslipidaemia, and hypertension occur with increased frequency
[4-6]. In addition, several medical conditions, such as poor pulmonary function, hepatic steatosis, sleep apnoea, and orthopaedic complications, are associated with obesity
[1,5,7,8]. These medical conditions often persist into adulthood and will result in substantial psychosocial and somatic morbidity, with loss of school or working days
[9].

Current treatments for obesity are lifestyle, drug, and surgical interventions
[10-12]. Behavioural lifestyle intervention can produce significant reduction of obesity in children and adolescents
[13]. However, the efficacy of lifestyle intervention programs on body mass index (BMI) and all related complications on the long-term are questionable, taking into account the high drop out and the frequent relapse of obesity in this group of patients. Therefore, in clinical practice, adding a pharmacological agent to conventional treatment is often considered. Three agents have been studied: orlistat, a gastrointestinal lipase inhibitor, sibutramine, a serotonin and noradrenalin re-uptake inhibitor, and metformin, an insulin sensitizing agent
[10-12,14]. Both orlistat and sibutramine have been shown to have an additional reducing effect on the absolute BMI in children and adolescents, yet medication-related adverse effects, such as tachycardia, hypertension, arrhythmia, and gastro-intestinal tract symptoms, were frequently reported
[11,15,16]. Efficacy of metformin was investigated in hyperinsulinemic, obese adolescents by Park et al. in a systematic review

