### Design

The metformin study is a multicentre study, divided in two parts, both of 18 months. The first part is a randomized, double-blind placebo controlled trial, with two parallel groups. At study entry, participants are randomized to metformin or placebo for 18 months. All participants will be offered a lifestyle intervention program. This program consists of supervised physical training twice weekly, and individual dietary advice during hospital visits. Participants will visit the hospital 9 times during this part of the study. Between these visits, monthly telephone calls are made.The second part of the study is an open label, follow-up study. Participants who remain obese and insulin-resistant at entrance of the second part, can choose between metformin treatment and no medication. Participants who do not meet these criteria, do not use medication in this part of the study. Therefore, after the follow-up study there are four arms: participants with metformin in both parts, metformin in part 1 and no medication in part 2, placebo in part 1 and metformin in part 2, and placebo in part 1 and no medication in part 2 (Figure 
1).

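### The efficacy model switches from repeated-measures GLM to a mixed model on an undefined amount of missing data; one mixed model should be fixed before unblinding

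*Protocol article*

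**What the plan says.** The section Efficacy of metformin names two routes to the same treatment comparison. The first is a two-group test: "To assess the effect of metformin versus placebo, the Students T test will be used to compare means of normally distributed data", with Mann-Whitney for data that are not normal. The second is longitudinal: "General linear models (analysis of repeated measures) or mixed models (if too much data is missing) will be used to determine the therapeutic effect". Neither is called primary. The section does not list the visits to be modelled, define how much missing data is excessive, or say when the choice between GLM and mixed model is made.

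Related statements elsewhere in the article:

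- Statistical analysis: "Data will be analysed using IBM SPSS Statistics".
- Design: "Participants will visit the hospital 9 times during this part of the study" (part 1).
- Physical examination and anthropometrics: "Every visit, except at week 3 and 5, anthropometric measurements are performed".
- Sample size, on HOMA-IR: "Group sample sizes of 60 patients in both groups were found sufficient for the detection of a difference of 1.6 with a significance level of" (the level printed there is 5%).
- Sample size, on dropout: "To prevent inadequate power due to drop out of participants, 20% more patients will be included".
- Breaking of the study blind: the blind is broken once every participant has completed part 1.
- Objectives: the primary objective concerns the effect at 18 months.

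**The concern.** Repeated-measures GLM in the named software needs a value at every occasion entered and removes a participant who lacks one. A mixed model fitted by likelihood uses every observed visit and is valid under the weaker assumption that data are missing at random. With complete data it gives nearly the same answer as GLM, so nothing is gained by holding it back as a fallback.

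The switch also depends on the accrued data and has no threshold. Together with a two-group test of unstated status, this leaves three candidate analyses of one primary comparison, and the printed text does not settle which of them counts.

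Two things are at stake. One is power: the 20% addition is there for dropout, and does not allow for participants who finish but are deleted for one missed visit. The other is bias, if those who miss visits or leave differ in outcome from those who attend throughout.

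**Working it through.** **1. The plan's own figure.** 60 × 1.20 = 72 per arm, and 2 × 72 = 144. This matches the stated total. The 60 per arm that HOMA-IR needs is left if 12 of 72 (16.7%) drop out; a 20% dropout leaves 72 × 0.80 = 57.6.

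**2. Number of occasions.** Nine part 1 hospital visits less weeks 3 and 5 leaves seven with anthropometrics: weeks 0, 13, 25, 37, 49, 61 and 73. Table 3 has fasting glucose and insulin, directly or as the first OGTT sample, at the same seven. Part 1 OGTTs fall at weeks 0, 37 and 73 only. So a GLM could plausibly use seven occasions (five intermediate) or three (one intermediate).

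**3. Complete cases.** Assume 60 per arm have weeks 0 and 73, and each of k intermediate visits is missed independently with probability m. Complete cases per arm = 60 × (1 − m)^k. The article gives no miss rate, so m is an assumption.

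- Seven occasions, k = 5: 60 × 0.95^5 = 46.4; 60 × 0.90^5 = 35.4.
- Weeks 0, 37 and 73, k = 1: 60 × 0.95 = 57.0; 60 × 0.90 = 54.0.

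**4. Indicative power.** The article gives no SDs and no HOMA-IR power. I back-solved the SDs from its own sample sizes, two-sided 0.05, with SD = difference / [(1.960 + z_power) × √(2/n)]:

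- BMI: 2.94 / [(1.960 + 1.282) × √(2/47)] = 4.40 percentage points.
- HOMA-IR: 1.6 / [(1.960 + 0.842) × √(2/60)] = 3.13 if power was 80%; with 1.282 in place of 0.842, 2.70 if it was 90%.

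Power = Φ[difference / (SD × √(2/n)) − 1.960]:

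| Occasions modelled | m | n per arm | HOMA-IR, if planned at 80% | HOMA-IR, if planned at 90% | BMI |
|---|---|---|---|---|---|
| All seven | 5% | 46.4 | 69% | 81% | 90% |
| All seven | 10% | 35.4 | 58% | 70% | 80% |
| 0, 37, 73 | 5% | 57.0 | 78% | 89% | 95% |
| 0, 37, 73 | 10% | 54.0 | 76% | 87% | 94% |

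These are powers of a two-group comparison at one time point with the reduced n. They show what the lost participants cost; they are not the power of the repeated-measures model itself.

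**5. Bias, one illustration.** A simulation took 72 per arm, a true week-73 difference of −0.67 SD, correlation 0.8 between adjacent visits, dropout more likely after a poor value, and 5% sporadic misses. Complete cases were 62% of participants. Their mean estimate was −0.643 (SD of estimates 0.204), against −0.668 (0.189) for likelihood using all observed data. The complete-case estimate was too small by 0.027, about 4% of the effect (0.027/0.67), and it was less precise. Other missingness patterns would give other figures.

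**The case against.** There is a good case that this should not be pressed too far, and much of it stands.

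- A reader might infer that GLM is the default primary analysis and discards everyone with one missed visit. The article does not say so. The t test and Mann-Whitney test come first, and a test at week 73 loses nobody for a missed week-25 visit. Deletion affects only the occasions entered, which are not listed; with weeks 0, 37 and 73 the loss is small.
- The worst power figures assume that the fallback is not used. At 10% misses over seven occasions, 41% of week-73 attenders are incomplete (1 − 0.90^5), and the mixed model might well be chosen then.
- A reader might infer from the Background that the plan expects dropout linked to relapse. The words are "taking into account the high drop out and the frequent relapse of obesity in this group of patients". They concern lifestyle programmes in general, list two facts without linking them, and do not forecast dropout in this trial, whose own allowance is 20%.
- The trigger is the amount of missing data, not the outcome values, and could be judged blind. Nothing in the article shows selection on results.
- A repeated-measures GLM can give a contrast at week 73. The article does not say that an effect averaged over visits will be used.
- A separate analysis plan could hold the threshold, visits and contrast.

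The last point does not remove the concern. The criticism is of a rule that is printed, not of missing detail. A threshold set elsewhere would still leave a data-dependent switch with the weaker longitudinal method first.

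**Conclusion.** The point holds as a should-fix. The article ties the choice of longitudinal model to an undefined amount of missing data, does not require that choice before unblinding, and does not rank it against the two-group tests. That follows from the text alone. Listwise deletion follows from the method and the named software; the article does not state it.

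The size is conditional. From 60 per arm, the loss to deletion runs from 3 per arm (three occasions, 5% misses) to about 25 (seven occasions, 10% misses). The lower end is minor. The upper end would take HOMA-IR power from an assumed 80% to about 58%, and BMI from its planned 90% to about 80%. These figures rest on assumed, independent miss rates, back-solved SDs and the fallback not being used. Bias is possible if missingness is related to outcome, but the article gives no basis for its size.

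**What to change.** Delete the GLM option and the missing-data trigger. Before the blind is broken, prespecify one likelihood-based mixed model for repeated measures for each primary endpoint, BMI standard deviation score and HOMA-IR (transformed if skewed). Include arm, visit, arm-by-visit interaction and baseline value, and use the model whatever the amount of missing data. Name the week-73 arm contrast as the primary estimate, and make the t test and Mann-Whitney test supportive only. A sensitivity analysis for data not missing at random would complete it.

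The cost is a change of wording in the protocol or analysis plan. Mixed models are already named there and are available in the stated software. No visit, measurement or participant is added. When the article was published, 60 participants had been included and 13 had finished part 1, so there was time to settle this before unblinding.

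### Repeated-measures GLM with a mixed model only as an undefined fallback makes the longitudinal efficacy analysis a complete-case analysis; the mixed model should be fixed in advance

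*Protocol article*

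**What the plan says.** The section Efficacy of metformin names two kinds of between-group analysis. The first is a simple comparison: "To assess the effect of metformin versus placebo, the Students T test will be used to compare means of normally distributed data", with the Mann-Whitney U test for nonparametric data. The second is longitudinal: "General linear models (analysis of repeated measures) or mixed models (if too much data is missing) will be used to determine the therapeutic effect". The section does not call either one primary, list the visits in the longitudinal model, define how much missing data is too much, or say when that is judged. The section Statistical analysis states "Data will be analysed using IBM SPSS Statistics".

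The Sample size section gives "a sample size of 47 participants per group (metformin and placebo) is sufficient to detect a change in BMI of 2.94% with 90% power". For HOMA-IR, where the level is set at 0.05, it says "Group sample sizes of 60 patients in both groups were found sufficient for the detection of a difference of 1.6 with a significance level of" (quotation cut before the figure). It then adds: "To prevent inadequate power due to drop out of participants, 20% more patients will be included", giving 144 in total, or 72 per arm. The Background describes long-term lifestyle programmes as "taking into account the high drop out and the frequent relapse of obesity in this group of patients", without a rate.

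According to Tables 2 and 3 and the section on physical examination, anthropometry and fasting glucose and insulin (directly or within the OGTT) are collected in part 1 at weeks 0, 13, 25, 37, 49, 61 and 73.

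**The concern.** The article does more than leave the model open. It states an order of preference: GLM first, mixed model only if a condition is met. Both parts of that rule are weak.

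- **Complete cases.** SPSS repeated-measures GLM needs a value at every modelled visit. A participant who misses one modelled interim visit but attends week 73 is removed, although the 18-month outcome is known. Those who remain are selected after randomisation by attendance. If attendance depends on response or tolerability, and does so differently by arm, the comparison is no longer the randomised one.
- **The switch.** Whether a complete-case result is biased depends on why values are missing as well as on how many are missing. A trigger based on amount alone therefore looks at the wrong thing. With no threshold and no decision time, it also leaves the model to be chosen after the data are in.

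At stake are the validity of the 18-month comparison and, for HOMA-IR, the power the trial was sized for. The 20% addition is described as cover for dropout; completers lost to listwise deletion are not mentioned.

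**Working it through.** **1. The plan's own figure.** 60 × 1.20 = 72 per arm, and 2 × 72 = 144. This reproduces the stated total.

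**2. Loss that the planned size can absorb under listwise deletion.** Total loss here means dropout plus any participant removed for a missed modelled visit.
- HOMA-IR: 1 − 60/72 = 16.7%.
- BMI: 1 − 47/72 = 34.7%.

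At exactly 20% total loss, 72 × 0.80 = 57.6 per arm remain: slightly under 60, well above 47.

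**3. Standardised effects implied by the plan.** No SD is given, and no power for HOMA-IR. I assume two-sided α = 0.05 and the normal approximation d = √(2/n) × (z₀.₉₇₅ + z_power).
- BMI, n = 47, 90% power: √(2/47) × (1.960 + 1.282) = 0.669.
- HOMA-IR, n = 60, if 80% was intended: √(2/60) × (1.960 + 0.842) = 0.511.
- HOMA-IR, n = 60, if 90% was intended: √(2/60) × (1.960 + 1.282) = 0.592.

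**4. Illustration.** Assume 60 per arm are seen at week 73, and that each of k modelled interim visits is missed independently with probability m. Complete cases per arm = 60 × (1 − m)^k. Power = Φ(d√(n/2) − 1.960), treating the test as a two-group comparison.

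| k | m | n per arm | HOMA-IR power (80% planned) | HOMA-IR power (90% planned) | BMI power |
|---|---|---|---|---|---|
| any | 0 | 60 | 80% | 90% | 96% |
| 1 (week 37) | 5% | 57.0 | 78% | 89% | 95% |
| 5 | 3% | 51.5 | 74% | 85% | 92% |
| 5 | 5% | 46.4 | 69% | 81% | 90% |
| 5 | 10% | 35.4 | 58% | 70% | 80% |

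Example: 60 × 0.95⁵ = 46.4; 0.511 × √23.2 − 1.960 = 0.50; Φ(0.50) = 69%. With 20% total loss and nothing further, HOMA-IR power is 78% (or 89%) and BMI power 95%.

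**5. Can the complete-case set be biased?** A simulation with no true effect used 72 per arm, six post-baseline visits and correlations from 0.78 (adjacent) to 0.61 (first to last). Metformin dropout followed a poor previous value (log-odds 1 per SD), while placebo dropout was random. At about 17–23% dropout the completers' week 73 difference favoured metformin by about 0.15 SD, and the t test's false-positive rate was about 13%. When the same dropout mechanism was applied in both arms, the bias vanished and the rate returned to 5%. So bias is possible, and its size depends on a mechanism that the documents do not describe.

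**The case against.** The strongest reply is that the article names the t test first and calls no analysis primary, while the objective is set at 18 months. A week 73 t test keeps a participant who missed an interim visit and loses only those without a week 73 value, which is what the 20% addition is for. This stands: GLM is the preferred longitudinal model, but the document does not make it the sole or primary efficacy analysis. The t test does not cure the problem, however, because it too leaves out every dropout.

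A reader might infer that anyone with a single missed visit is lost and that the analysis will necessarily fall below the planned size. The documents do not support that. Only visits in the model matter, and none are listed; a model on weeks 0, 37 and 73 loses far fewer. For BMI the margin is wide, and even the 5% case above leaves power at about 90%. At the heaviest missingness the plan's own fallback to a mixed model might be used.

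A reader might also infer a specific inflated error rate or deliberate model selection. Neither follows. The simulated bias needs dropout that differs by arm. The stated trigger is the amount of missing data, not the effect, and could be judged blind, since staff stay blinded until all participants finish part 1. What remains is that nothing in the text requires the choice to be made then.

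Finally, the visit list and covariance structure may sit in an analysis plan that is not shown. That is fair, and their absence is not the point here. The point is the rule that the article does state.

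**Conclusion.** The concern holds as a should-fix. As written, the longitudinal analysis prefers a method that discards randomised participants with usable 18-month data, and turns to the better method only on an undefined trigger. The complete-case set can be biased if missingness relates to response or tolerability. It can fall below 60 per arm for HOMA-IR above 16.7% total loss; BMI stays at or above 47 per arm up to 34.7%.

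The two thresholds follow from the plan's own numbers. The drop in HOMA-IR power from 80% to about 69% rests on assumptions: 80% planned power, two-sided testing, 60 per arm at week 73, five modelled interim visits and 5% missed at random at each. The size and direction of any bias cannot be stated from the documents.

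**What to change.** In Efficacy of metformin, delete the GLM option and the condition about too much missing data. Specify, before unblinding, a likelihood-based mixed model for repeated measures:

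- all randomised participants with available data, whatever the amount missing;
- visit as a factor, with treatment by visit;
- the treatment effect taken as the 18-month contrast;
- HOMA-IR transformed if it is skewed.

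List the modelled visits, and keep the week 73 t test or Mann-Whitney test as a supportive analysis.

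The cost is about a sentence of text. SPSS has a mixed-model procedure, the visits are already scheduled, and essentially nothing is lost if the data turn out complete. When the article was written, 13 of the 60 included participants had finished part 1 and the blind was to hold until all had done so, so the change could still be made before any unblinded result. The model relies on missingness being explained by the observed data, and participants with no post-baseline value add little to it.
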